**Methods and analysis:**

This study is a multicentre, randomized, controlled clinical trial involving 84 patients diagnosed with OICPN. Participants will be randomly divided into two groups in a 1:1 ratio to receive either standard care alone or warm acupuncture plus standard care. This regimen will include 16 sessions, with treatments occurring twice a week for the first month and once a week for the subsequent 2 months. All participants will complete the 12-week program and one-year follow-up. Outcomes will be assessed by blinded evaluators. The primary outcome is neurotoxicity graded by the National Cancer Institute Common Terminology Criteria for Adverse Events (NCI-CTCAE) version 4.0. Secondary outcomes include the European Organization for Research and Treatment of Cancer Quality of Life Questionnaire–Chemotherapy-Induced Peripheral Neuropathy 20-item scale (EORTC QLQ-CIPN20) and the European Organization for Research and Treatment of Cancer Quality of Life Core 30 Questionnaire (EORTC QLQ-C30), measured at baseline, week 2, month 1, post-treatment, and during follow-up.

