### Sample size calculation

2.4

This study employs a randomized controlled trial methodology to assess the effectiveness of warm acupuncture for alleviating peripheral neuropathy caused by oxaliplatin, comparing a warm acupuncture cohort with a standard care cohort. The main measure of interest is the neurotoxicity level, which will be evaluated using the NCI-CTCAE version 4.0 criteria. Based on previous research, a treatment response is indicated by a decrease of one or more grades in neurotoxicity (37). The expected response rates for the two groups are 0.8 and 0.47, respectively. Utilizing a standard formula for the comparison of two proportions, with a two-tailed alpha level of 0.05 and a power of 80% (*β* = 0.2), a minimum of 33 participants is necessary for each group. Considering an estimated dropout rate of approximately 20%, the target sample size is established at no less than 40 participants per group. Consequently, the overall sample size for this investigation is set at 84 participants, with 42 in each group.

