### Statistical methods

4.2

Analysis of Baseline Characteristics: The baseline characteristics of each group will be delineated using appropriate summary statistics. For normally distributed continuous variables, the results will be shown as means ± standard deviations, with independent sample t-tests utilized for comparisons between groups. If the distribution is not normal, these variables will be reported as medians (interquartile ranges) and analyzed using the Mann–Whitney U test. Categorical data will be reported as frequencies (percentages) and analyzed for differences between groups using either the Chi-square test or Fisher’s exact test, depending on the situation.

Analysis of the Primary Outcome: The primary focus will be on the ordinal categorical variable representing the neurotoxicity grade according to NCI-CTCAE version 4.0. A Generalized Estimating Equations (GEE) approach or a mixed-effects ordinal logistic regression model will be utilized to analyse the primary outcome. This model will be used to conduct a statistical assessment comparing the effectiveness of warm acupuncture with alternative treatments, emphasizing differences between groups, temporal effects, and their interactions to determine its role in reducing neurotoxicity.

Analysis of the Secondary Outcomes: Secondary outcomes, which include the continuously measured scores from the EORTC QLQ-CIPN20 and the commonly used EORTC QLQ-C30 scales, will be analyzed using a linear mixed-effects model. This model will incorporate fixed effects for group, time, visit, and the interaction between group and time, while subject will be treated as a random effect. This approach aims to assess the variations in symptom burden and quality of life across groups and their changes over time.

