Additional statistical details are predefined. In the primary models, we will adjust for key baseline covariates that display an imbalance (*p* < 0.1) or possess established prognostic significance (e.g., number of chemotherapy cycles). If a significant group-by-time interaction is identified, Bonferroni-corrected *post hoc* pairwise comparisons will be conducted. Missing data, assumed to be missing at random, will be managed using the likelihood-based estimation inherent to linear mixed models; the robustness of findings will be assessed through sensitivity analyses, including the last observation carried forward method. All adverse events will be summarized using descriptive statistics, and between-group differences in incidence rates will be evaluated using the Chi-square test or Fisher’s exact test, as appropriate. For participants who withdraw from the study, the primary efficacy analysis will follow the Intention-to-Treat (ITT) principle, with linear mixed models handling missing data under the Missing at Random assumption. A Per-Protocol (PP) analysis will be conducted as a sensitivity measure. All withdrawals and protocol deviations will be recorded with detailed reasons.

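### The mixed model listed for QLQ-CIPN20 and QLQ-C30 neither adjusts for the baseline score nor gives the arms a common baseline mean, so the secondary contrasts are less precise than the collected data allow

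*Protocol article*

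**What the plan says.** Section 4.2 (Statistical methods) gives the model for the continuous secondary scores explicitly. It has "fixed effects for group, time, visit, and the interaction between group and time", and "subject will be treated as a random effect".

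The abstract has both questionnaires "measured at baseline, week 2, month 1, post-treatment, and during follow-up". Table 1 shows them at T0 and at eight later visits, T1 to T8 (weeks 2 to 60).

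Two further sentences in section 4.2 bear on the point. The covariate rule reads "In the primary models, we will adjust for key baseline covariates that display an imbalance" at p < 0.1, or that have established prognostic significance; its example is the number of chemotherapy cycles. The rule for follow-up tests begins "If a significant group-by-time interaction is identified, Bonferroni-corrected" and goes on to pairwise comparisons, without saying whether these compare visit means or changes from baseline.

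The article does not say whether T0 is part of the response vector. It gives no standard deviation or correlation for either scale.

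**The concern.** Randomisation makes the expected T0 scores of the two arms equal. A model with T0 in the response, a free group term and group-by-time does not use that fact: it estimates a separate T0 mean for each arm. The treatment contrast is then either a difference in change from baseline, which uses the baseline score but not optimally, or a difference in visit means, which in effect ignores it. If T0 is left out of the response, the listed model ignores the baseline score altogether. On every one of these readings the contrast has a larger variance than it needs to have.

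At stake is the precision of the CIPN20, the trial's dedicated patient-reported neuropathy scale, and of the C30 scores. The trial has 84 patients, is sized only for a responder comparison on the CTCAE grade, expects about 20% dropout and plans Bonferroni-corrected comparisons, so there is little precision to spare on these scores.

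**Working it through.** **The plan's own figure.** Section 2.4 states "The expected response rates for the two groups are 0.8 and 0.47, respectively" with a "two-tailed alpha level of 0.05 and a power of 80"%. The pooled two-proportion formula without continuity correction gives 33 per group, as stated. That calculation concerns the responder comparison only. The article gives no variance or power figure for the secondary scores, so there is nothing to reproduce for them.

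**Inputs.** From the documents: nine visits (Table 1), 1:1 allocation, a random subject effect (read as a random intercept, so compound symmetry) and the listed fixed effects. Assumed: a baseline-to-follow-up correlation ρ, with 0.4–0.7 as the working range and 0.3 and 0.9 as outer values; a separate group effect at each visit; complete data.

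**Formulas for one follow-up visit**, with n per arm and score variance σ²:

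- Difference in change, free T0 means: 4σ²(1 − ρ)/n
- Difference in visit means: 2σ²/n
- Baseline-adjusted, or common T0 mean: 2σ²(1 − ρ²)/n

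The variance ratios against the third line are 2/(1 + ρ) for change and 1/(1 − ρ²) for visit means. Both exceed 1 for any ρ strictly between 0 and 1. Generalised least squares with all nine visits gives the same values.

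| ρ | Change: 2/(1 + ρ) | Visit means: 1/(1 − ρ²) |
|---|---|---|
| 0.3 | 1.54 | 1.10 |
| 0.4 | 1.43 | 1.19 |
| 0.5 | 1.33 | 1.33 |
| 0.6 | 1.25 | 1.56 |
| 0.7 | 1.18 | 1.96 |
| 0.9 | 1.05 | 5.26 |

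For ρ of 0.4–0.7 the excess variance is therefore 18–43% for change and 19–96% for visit means. In standard errors (square roots) this is about 8–20% and 9–40%. When ρ is high the change contrast loses little and the visit-mean contrast loses most. Because the plan names neither, it does not secure the better case.

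**Average over the eight post-baseline visits.** Write m = (1 + 7ρ)/8. The ratio is (1 + m − 2ρ)/(m − ρ²) for change and m/(m − ρ²) for means. At ρ = 0.5, m = 0.5625 and both ratios are 0.5625/0.3125 = 1.80. At ρ = 0.7, m = 0.7375, and they are 0.3375/0.2475 = 1.36 and 0.7375/0.2475 = 2.98.

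**Single linear slope.** If time is linear, visit categorical, and group-by-time one slope over the Table 1 weeks, the excess variance of that slope with a free rather than zero arm difference at T0 is about 14%, 10%, 7% and 4% at ρ = 0.4, 0.5, 0.6 and 0.7.

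**What this means in power, for illustration only.** Suppose the listed analysis had 80% power at one visit. With a variance ratio R, the baseline-adjusted analysis would have power Φ(2.80√R − 1.96). For R = 1.18 to 1.43 this is 86–92%; for R = 1.19 to 1.96 it is 86–98%. The trial sets no such power for these scores.

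**The case against.** The strongest reply is that this is a conventional model, unbiased under randomisation and data missing at random, and that baseline coding and contrasts are often settled in an analysis plan, which is not shown here. The unbiasedness stands: this is not an error of validity, and the primary outcome is untouched. The appeal to an unseen plan is weaker, because the article lists the fixed effects and introduces its further details as predefined.

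Second, the covariate rule may reach further than it seems. The words "In the primary models, we will adjust for key baseline covariates" use a plural that is not defined, and the same paragraph ties the primary efficacy analysis to linear mixed models, which section 4.2 specifies only for the secondary scores. A reader might infer that baseline adjustment is ruled out for CIPN20 and C30; the text does not support that. Even on the broad reading, though, the baseline score would enter only through an observed imbalance or a judgement about prognosis.

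Third, the size. A reader might infer one fixed loss, but no correlation, contrast or target visit is given, and the list names time and visit separately, so a linear-slope reading with a smaller loss is open. It is also easy to quote the saving as the excess: for change, the saving is (1 − ρ)/2, or 15–30% at ρ of 0.7 down to 0.4, whereas the excess is 18–43%.

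Finally, a reader might say that the baseline data are discarded. That is wrong for the change contrast, which uses them, though not optimally.

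**Conclusion.** The point holds as a loss of precision in the secondary analyses. The listed model makes no use of the equality of the T0 means and does not adjust for the baseline score, and the covariate rule does not reliably close the gap. The direction does not depend on whether T0 is in the response, and it holds for every ρ strictly between 0 and 1. The size does depend on assumptions: about 18–43% excess variance for a difference in change and 19–96% for a difference in visit means, given ρ of 0.4–0.7, a separate group effect at each visit and complete data; about 4–14% for a single linear slope over the same ρ. None of these figures can be derived from the article alone. They do not imply bias, and they do not touch the primary conclusion.

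**What to change.** State one of the following for CIPN20 and for every C30 score:

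1. Keep T0 in the response, give both arms a common T0 mean, and fit group-by-visit terms at T1 to T8 only.
2. Take T0 out of the response and enter the patient's baseline score with its interaction with visit.

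The two are similar but not identical. Under a random intercept the first imposes one variance and one correlation at all visits, while the second lets the baseline slope differ by visit; they also differ when T0 or follow-up scores are missing. So choose one in advance. In the same sentence, name the treatment contrast and its visit, and say whether group-by-time means a separate effect at each visit or a linear slope. Also say whether the covariate rule applies to the secondary models.

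The cost is a line or two of analysis text. No new data are needed, and either form is valid under randomisation.

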### Study design

2.1

This clinical trial is designed as a randomized, controlled study with the assessors blinded to the treatment allocation. It will be conducted in six medical facilities throughout China, including the Jiangsu Province Hospital with Integration of Chinese and Western Medicine, Huai’an Hospital of Traditional Chinese Medicine, Yancheng Hospital of Traditional Chinese Medicine, Jiangyin Hospital of Traditional Chinese Medicine, Dongtai Hospital of Chinese Medicine, and Nanjing Lishui District Hospital of Traditional Chinese Medicine. The recruitment of participants will occur simultaneously in outpatient settings and hospital wards.

The Institutional Ethics Committee at the coordinating centre has reviewed and granted approval for this study, as indicated by the approval number 2024-LWKYZ-008, which remains valid until February 23, 2027. Prior to participation, all individuals will provide written informed consent. Participants who are enrolled will receive complimentary warm acupuncture treatment. The methodology in this trial is meticulously organized, ensuring that ethical standards are met. The protocol aligns with the Standard Protocol Items: Recommendations for Interventional Trials (SPIRIT) guidelines to uphold scientific integrity (35). Additionally, the results will be reported in accordance with the relevant Consolidated Standards of Reporting Trials (CONSORT) extension guidelines, ensuring rigorous quality control throughout the research (36).

Participants who meet the criteria will be randomly divided into two groups, with an equal ratio of 1:1, assigning them to either the warm acupuncture group or the standard care group. All individuals will participate in a treatment phase lasting 12 weeks, followed by a follow-up period of 1 year. Medical statisticians will analyse the outcome data. This trial has been officially registered with the Chinese Clinical Trial Registry (Registration number: ChiCTR2400082506). The flow of this study is illustrated in Figure 1, while a comprehensive schedule for enrolment, interventions, and assessments is provided in Table 1.

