### Randomization and allocation concealment

2.5

A statistician who is not part of the clinical trial will create the randomization sequence utilizing SAS software, version 9.4 (SAS Institute Inc., Cary, NC, United States). This sequence will utilize a block randomization approach with block sizes of 4, 6, or 8, organized by study centre. The resulting randomization list will then be uploaded to an Interactive Web Response System (IWRS). After screening an eligible participant and obtaining informed consent, the site investigator will access the IWRS to enter the participant’s basic identifiers along with the centre code. The system will then automatically generate a unique randomization number and assign the appropriate treatment group, ensuring that allocation remains fully concealed. Regular audits of IWRS procedures and documentation will be conducted to ensure consistent implementation of the allocation workflow across all centers.

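### The p<0.1 baseline screen makes the primary model depend on chance imbalance; a fixed set with centre and baseline grade should replace it

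*Protocol article*

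**What the plan says.** The rule is in section 4.2 (Statistical methods), in the paragraph of additional details that the article describes as predefined. Of the primary models it says "we will adjust for key baseline covariates that display an imbalance", and it gives two routes into the model, joined by an or: covariates that "display an imbalance (*p* < 0.1) or possess established prognostic significance (e.g., number of chemotherapy cycles"). The between-arm baseline tests that would feed the first route (t, Mann-Whitney, chi-square or Fisher) are set out earlier in the same section.

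For the primary outcome the article says "A Generalized Estimating Equations (GEE) approach or a mixed-effects ordinal logistic regression model will be utilized to analyse the primary outcome". It describes that model as "emphasizing differences between groups, temporal effects, and their interactions". Neither place names centre or baseline grade.

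Section 2.5 gives a "block randomization approach with block sizes of 4, 6, or 8, organized by study centre". On the number of centres, section 2.1 says "It will be conducted in six medical facilities throughout China". Section 2.2 admits patients at CTCAE grade 2 or higher, and Table 1 records the grade at T0.

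**The concern.** After concealed, computer-generated allocation, any baseline difference between the arms is chance. A significance test on it therefore says nothing about whether the variable needs adjustment. What matters is whether the variable predicts outcome, and the p<0.1 route does not ask that. Its practical result is that part of the primary model is settled by the trial's own data.

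The same route is also badly aimed. Centre has a design claim to be in the model because it stratifies the randomisation. Baseline grade has a prognostic claim because patients enter at different grades and section 2.4 counts response as a fall from the starting grade. The screen is poorly suited to picking up either. At stake are a primary estimate that readers can trust as fixed in advance, and power that the trial could have at no cost in patients.

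**Working it through.** **1. The plan's own figure.** Section 2.4: response rates 0.80 and 0.47, two-sided alpha 0.05, power 80%. With pooled variance under the null, the mean rate is 0.635 and n = [1.96·√(2·0.635·0.365) + 0.842·√(0.8·0.2 + 0.47·0.53)]² / 0.33² = 32.2, so 33 per group. Then 33/0.8 = 41.25, so 42 per group and 84 in total. Both stated figures reproduce, and nothing below changes them.

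**2. Chance entry through the p<0.1 route.** Each covariate passes with probability 0.1 under randomisation. For k independent covariates, P(at least one enters) = 1 − 0.9^k: k=3 gives 27%, k=5 gives 41%, k=10 gives 65%. The article gives no k, so k is an assumption.

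**3. Could the screen admit centre?** Assume six equal centres of 84/6 = 14. With a largest block of 8, the arms within a centre cannot differ by more than 4. Put that maximum in every centre, in opposite directions so that the arms stay equal overall: chi-square = 6 × 4²/14 = 6.86 on 5 df, p = 0.23. Under these assumptions centre cannot reach p<0.1. Very unequal centres could behave differently.

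**4. Could it admit baseline grade?** Only by chance, about 10% of the time. In the simulation below it entered in 9% to 11% of trials.

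**5. Indicative simulation.** Setting: 84 patients, six centres of 14 with seven per arm, one binary response, no dropout, 2,500 runs per row. Control log odds are ln(0.47/0.53) = −0.12. The treatment log odds ratio is ln(0.8/0.2) − ln(0.47/0.53) = 1.51. One prognostic covariate is always in the model, standing in for chemotherapy cycles. Five candidates are screened at p<0.1: grade and four pure-noise variables. The grade and centre effects are assumptions; the article gives none. Centre is fitted as fixed effects in the comparison model.

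| Grade log OR, centre SD | Type I error: rule | Type I error: grade + centre | Power: rule | Power: grade + centre | Mean log OR: rule | Mean log OR: grade + centre |
|---|---|---|---|---|---|---|
| 0, 0 | 4.8% | 5.5% | 88.6% | 90.0% | 1.60 | 1.75 |
| −1, 0.5 | 3.9% | 5.2% | 83.2% | 86.8% | 1.46 | 1.76 |
| −2, 0.5 | 3.8% | 5.3% | 72.3% | 81.2% | 1.28 | 1.78 |
| −2, 1.0 | 3.2% | 5.5% | 66.7% | 78.4% | 1.20 | 1.81 |

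The Monte Carlo error on a 5% rate is √(0.05·0.95/2500) = 0.4 points. The power differences in the last three rows are 3.6, 8.9 and 11.7 points. With grade prespecified but centre left out, type I error in those rows stays at 3.5% to 3.9%, so the conservatism comes from omitting centre. Power with grade alone is 85.2%, 78.9% and 72.4%, so both variables contribute to the gain.

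The standard error does not shrink with adjustment. Under the null in the third row its mean is 0.47 under the rule and 0.55 with grade and centre. The gain comes from a less attenuated odds ratio and from restoring the test to its nominal size.

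The last column exceeds the true 1.51 in every row, including the row with no centre effect. That is sparse-data bias from fixed centre effects, and it bears on how centre should be fitted.

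**6. Does leaving out centre cut the planned 80%?** Section 2.4 uses overall response rates, so its variance already contains any between-centre part. With allocation balanced within centres, the unadjusted test has power of approximately Φ(0.842/√(1 − ICC)): 80.6% at an ICC of 0.05 and 81.9% at 0.15 (assumed values). It does not fall below 80%.

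**The case against.** The strongest reply is that this is a condensed article. A full covariate list, stratification factors included, commonly sits in an analysis plan that is not shown. The prognostic route is open-ended, so baseline grade could enter by it, or could already be in the model as the T0 response, since Table 1 measures grade at every visit. This stands. A reader might infer that centre and baseline grade are excluded from the model; the article supports only that they are not named, and that alone would be no finding. The reply does not reach the p<0.1 route, which is stated outright and is not cancelled by an alternative joined with an or. A later analysis plan could remedy it only by departing from the published rule.

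Three other inferences are tempting and fail:

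- That a data-driven model inflates the false-positive rate. The simulation shows the opposite when centre matters: 3.2% to 3.9%.
- That power falls below plan because centre is ignored. Step 6 shows it does not. The 67% and 72% in the table are not comparable with the planned 80%: they take 1.51 as a conditional log odds ratio alongside strong assumed grade effects, so the overall effect there is smaller than 0.80 against 0.47.
- That the estimate has too large a standard error. That is linear-model reasoning and does not carry over to the logistic models planned here.

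It is also fair to say that a chance covariate entering does little harm in itself, and that fixed effects for six centres in 84 patients carry their own risk. Both are accepted; the second shapes the fix.

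**Conclusion.** The point holds in a limited form. The stated p<0.1 route makes the primary model data-dependent in a paragraph that calls its details predefined, and it selects on chance: 27% to 65% probability of at least one chance entry for 3 to 10 independent candidates. It would seldom admit centre or baseline grade, neither of which is named. If those variables predict outcome, leaving them out makes the test conservative, pulls the odds ratio towards 1 relative to the conditional value, and forgoes about 4 to 12 points of power. If they do not, almost nothing is lost (about 1 point).

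The sizes rest on assumed grade and centre effects and on a single binary visit without dropout, not the planned repeated ordinal model, so they are indicative. If GEE is chosen, the attenuated odds ratio is partly a different (population-averaged) quantity rather than a biased one; the objection to choosing covariates by a baseline test is the same. This should be changed, but it does not threaten the validity of the trial.

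**What to change.** Delete the p<0.1 criterion. In its place, fix the adjustment set before any comparative data are seen:

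- **Centre**, as a random intercept, or with small centres pooled by a stated rule, to avoid the sparse-data bias of six fixed effects in 84 patients.
- **T0 grade**, either as a covariate or as the T0 response in a model that constrains the arms to a common baseline. State which. Use the T0 score of the same scale in the secondary models.
- **Number of chemotherapy cycles**, which the article already gives as prognostic.

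The cost is about one sentence and slightly more modelling work. The centre code is entered at randomisation and T0 grade is already scheduled, so there is no new data collection and the sample size stays at 84. The remaining downside is some sparse-data risk if centre is nevertheless fitted as fixed effects.

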### Warm acupuncture group

3.2

Alongside standard care, patients will receive warm acupuncture therapy. They will lie on their backs with the treatment areas properly exposed and sanitized. Acupuncture will be applied to the following specific points: Quchi (LI11), Waiguan (TE5), Hegu (LI4), and Baxie (EX-UE9) on the arms; Guanyuan (CV4) on the abdomen; and Zusanli (ST36), Sanyinjiao (SP6), Taichong (LR3), and Bafeng (EX-LE10) on the legs. A qualified practitioner with 3 years of experience will perform needling using single-use stainless steel needles (0.25 mm × 40 mm, sourced from Suzhou Hualun Medical Apparatus Co., Ltd., China). The insertion depth and angle will follow the guidelines in The Science of Acupuncture, utilizing a consistent reinforcing–reducing technique to prioritize patient safety and treatment efficacy. Once the deqi sensation is achieved, a 27-mm moxa stick (from Nanyang Baicaotang Natural Moxa Products Co., Ltd., made from 10-year aged moxa, measuring 18 mm × 27 mm) will be placed on the needle handles at Zusanli (ST36) and Guanyuan (CV4). The moxa stick will be held approximately 20 mm above the skin, separated by a small paper sheet. The base of the moxa stick will be ignited and allowed to burn out completely, after which the paper will be removed while the moxa remains on the needle. The needles will generally remain in place for 20 to 30 min before the ash is cleared and the needles are removed. This treatment will occur twice weekly during the first 4 weeks and once weekly from weeks five to 12, with each session lasting 30 min, completing a full 12-week course. This tapered frequency schedule was designed to achieve rapid symptom control during the initial intensive phase and to consolidate therapeutic effects during the subsequent maintenance phase.

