This study utilizes a multicentre, randomized controlled approach to apply a standardized warm acupuncture treatment in conjunction with standard care. The choice of acupoints is based on principles from The Science of Acupuncture, clinical experience, and data mining studies that identify frequently utilized point patterns for chemotherapy-induced peripheral neuropathy (39, 40). The selection process incorporates both local and distal point combinations. For the upper limbs, points like Quchi (LI11) and Waiguan (TE5) were chosen to facilitate meridian flow, while lower limb points such as Zusanli (ST36) and Sanyinjiao (SP6) were selected to balance qi and blood. Guanyuan (CV4) was included to strengthen the foundation and stabilize the source. The focused use of warm acupuncture at Guanyuan (CV4) and Zusanli (ST36) merges the therapeutic effects of acupuncture with the warming and circulation-boosting properties of moxibustion. The heat from the burning moxa penetrates deeper tissues through the needle, enhancing therapeutic effects that involve warming yang, boosting qi, and nourishing the meridians, thus creating a synergistic relationship between needling and moxibustion. From a neurobiological perspective, the therapeutic effects of warm acupuncture on CIPN may be mediated through multiple mechanisms that directly address the key pathophysiological processes of this condition. The thermal and mechanical stimulation generated by warm acupuncture can improve local microcirculation and increase blood supply to peripheral nerves, thereby counteracting the ischemic and metabolic disturbances that contribute to axonal degeneration. In addition, acupuncture-induced afferent input has been shown to activate descending serotonergic and noradrenergic inhibitory pathways, which suppress spinal nociceptive transmission—a mechanism similar to that of duloxetine, the currently recommended pharmacotherapy for CIPN (41). Preclinical evidence also suggests that acupuncture can reduce neuroinflammation by attenuating spinal glial cell activation and the release of pro-inflammatory cytokines (TNF-*α*, IL-1β, IL-6) that sensitize peripheral nociceptors (42, 43), and may modulate ion channel function, including voltage-gated sodium channels and TRPA1 channels, thereby reducing neuronal hyperexcitability and cold hypersensitivity (44, 45). Furthermore, by promoting mitochondrial function and enhancing neurotrophic support, warm acupuncture may facilitate axonal repair and regeneration (46, 47). While these mechanistic hypotheses require future validation, they provide a plausible neurobiological framework that complements the traditional Chinese medicine rationale for warm acupuncture in CIPN treatment. A consistent needling technique, moxa type, and treatment protocol were employed for all participants to address the variability that is often observed in acupuncture studies. Additionally, all procedures were conducted by certified acupuncturists to reduce the influence of practitioner differences on the results. Notably, this study included several follow-up assessments over a 12-month duration. This design facilitates the evaluation of both the immediate effects of warm acupuncture and a thorough investigation of its long-term effects on neurological recovery and improved quality of life. The outcome measures encompass both clinician-assessed scales and patient-reported outcomes, providing a comprehensive evaluation that spans from objective neurotoxicity assessments to subjective sensory experiences and improvements in quality of life. This approach aims to comprehensively assess the therapeutic outcomes of warm acupuncture.

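### Making visit-level comparisons depend on a significant group-by-time interaction can leave the week-12 and week-60 questions unanswered when benefit is early and sustained

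*Protocol article*

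**What the plan says.** In 4.2 Statistical methods, the primary ordinal model (GEE or mixed-effects) is described as "emphasizing differences between groups, temporal effects, and their interactions to determine its role in reducing neurotoxicity". No single visit or contrast is named as deciding. For the secondary scales, "This model will incorporate fixed effects for group, time, visit, and the interaction between group and time". The paragraph of additional details then sets the rule: "If a significant group-by-time interaction is identified, Bonferroni-corrected *post hoc* pairwise comparisons will be conducted". It is not limited to the primary outcome, so it appears to cover the secondary scales as well.

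Two other sections bear on it. Section 3.2 says the treatment schedule was "designed to achieve rapid symptom control during the initial intensive phase and to consolidate therapeutic effects during the subsequent maintenance phase". The Discussion says of the repeated follow-up: "This design facilitates the evaluation of both the immediate effects of warm acupuncture and a thorough investigation of its long-term effects". Table 1 schedules assessments at weeks 0, 2, 4, 8, 12, 16, 24, 36 and 60, so there are eight post-baseline visits.

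**The concern.** A group-by-time interaction has as its null hypothesis that the between-arm difference is the same at every modelled time. If only post-baseline visits are modelled, a benefit that is fully present at the first visit and then held satisfies that null exactly, however large it is. Early control followed by consolidation is close to the pattern the schedule aims for.

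If the condition is not met, the plan provides no between-group comparison at the end of treatment or at one year. The overall group term may be clearly significant, but it averages over visits and cannot say when benefit starts or whether it lasts. Comparing the arms at week 60 anyway would then go beyond what was prespecified.

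The rule is written out in full, so this is not a detail left to an analysis plan.

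**Working it through.** **Sample size first.** Inputs from 2.4: "The expected response rates for the two groups are 0.8 and 0.47, respectively", two-sided alpha 0.05, power 80%. With pooled variance and mean proportion 0.635:

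n = [1.960·√(2·0.635·0.365) + 0.842·√(0.80·0.20 + 0.47·0.53)]² / 0.33² = 32.2, rounded up to 33.

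This matches "a minimum of 33 participants is necessary for each group". Then 33/0.80 = 41.25, rounded up to 42 per arm, 84 in total. The sample size is not at fault.

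**Effect on a continuous scale (assumption).** Probit difference: 0.842 − (−0.075) = 0.917 SD.

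**Chance that the interaction is significant at 0.05.** Assumptions not in the document: compound symmetry, unit variance at each visit, correlation ρ = 0.5-0.7, complete data. Let δ_j be the arm difference at visit j, k the number of modelled visits and n the number per arm.

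- Categorical time: λ = (n/2)·Σ(δ_j − δ̄)²/(1 − ρ), with k − 1 and (2n − 2)(k − 1) df.
- Linear time in weeks w: λ = (n/2)·[Σ(w_j − w̄)δ_j]² / [Σ(w_j − w̄)²·(1 − ρ)], with 1 and (2n − 2)(k − 1) df.

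With n = 42, ρ = 0.5 and 0.917² = 0.841, the multiplier (n/2)/(1 − ρ) is 42:

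- T0 not in the response, full benefit from week 2: all δ_j equal, λ = 0.
- T0 not in the response, half benefit at week 2 and full from week 4: Σ(δ_j − δ̄)² = 0.841·0.25·7/8 = 0.184, λ = 7.7.
- T0 not in the response, linear build to week 12, then held: 0.841·0.830 = 0.698, λ = 29.3.
- T0 in the response, linear time, full from week 2: w̄ = 18, Σ(w_j − w̄)² = 3040, 0.841·18²/3040 = 0.0896, λ = 3.8.
- T0 a level of categorical time, full from week 2: 0.841·8/9 = 0.747, λ = 31.4.

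Noncentral-F power over ρ = 0.5-0.7:

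| Model and shape of benefit | 42 per arm | 33 per arm |
|---|---|---|
| T0 out, full by week 2 | 5% | 5% |
| T0 out, half at week 2, full from week 4 | 48-74% | 38-61% |
| T0 out, builds to week 12, then held | about 99% or more | 96% to over 99% |
| T0 in, linear time, full by week 2 | 49-71% | 40-60% |
| T0 in, categorical time, full by week 2 | about 99% or more | 96% to over 99% |

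**Unconditional comparison at one visit.** Two-sided alpha 0.05/8 = 0.00625. With noncentrality 0.917·√(42/2) = 4.20 on 82 df, power is about 91%; at 33 per arm it is about 81%.

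**Checks on ordinal grades.** In 1000 simulated trials (random-intercept cumulative logit, SD 2, 42 per arm, response 0.47 vs 0.80 at all eight post-baseline visits), the interaction was significant in 4.4% and the group term in 99.5%. A second simulation (3000 runs per setting, latent shift 0.8, response about 0.55 vs 0.82) gave 5-6% with T0 out, and 79% (33 per arm) or 91% (42 per arm) with T0 in as a categorical level.

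**The case against.** **The efficacy test is not conditional.** This stands. The group difference is assessed in its own right, and a constant effect is what a group term summarises. A reader might infer that the trial could miss a working treatment because of this rule; the document does not support that.

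**T0 may well be part of the response.** The abstract, section 3.3 and Table 1 list baseline alongside the later assessments, section 2.4 defines response as a fall in grade, and baseline grade is not named as a covariate. If T0 is a level of categorical time, a sustained benefit is itself a departure from parallel and the condition is nearly always met at the planned effect. A reader might infer that the interaction says nothing about whether warm acupuncture works; under this reading that is false. But the article does not commit to it. Eligibility requires grade 2 or more, so grades 0-1 cannot occur at T0, which sits awkwardly in an ordinal response model; this argument does not extend to the secondary scales. The secondary model also lists time and visit separately and attaches the interaction to time, which leaves linear time open.

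**The 5% figure is an extreme.** This stands too. It needs the full effect after two weeks of a twelve-week course, while the intensive phase lasts four weeks.

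**Convention and wording.** Testing the interaction before simple effects is common practice and contradicts nothing in the article. The rule does not forbid reporting visit-level estimates, and it does not define which pairs are compared. Between arms by visit is the natural reading; if only times within an arm were meant, no between-arm visit comparison would be planned at all.

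**Error control.** Bonferroni over eight visits protects those eight contrasts, but not those eight together with the overall group test. This stands and shapes the fix.

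**Conclusion.** The concern holds in a limited form. The interaction is a poorly chosen condition for visit-level comparisons: at the planned effect, its chance of being met runs from about 5% to about 99%, depending on unstated modelling choices and on how quickly benefit appears. An unconditional comparison at a given visit would have about 91% power at 42 per arm, or 81% at 33. At stake are the end-of-treatment and one-year answers that the Discussion promises; the overall efficacy conclusion and the sample size are unaffected. The figures rest on the probit conversion, compound symmetry with correlation 0.5-0.7, and complete data. None of these comes from the document.

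**What to change.** In the additional-details paragraph of 4.2, delete the opening conditional clause of the sentence. State instead that:

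- between-group contrasts at each post-baseline visit, including weeks 12 and 60, will be estimated from the fitted model with 95% CIs whatever the interaction p-value;
- they will be Bonferroni-corrected over the eight post-baseline visits;
- they are supportive of the overall group test and not a second route to the primary claim;
- the interaction test will be reported as a description of how the effect changes over time.

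The cost is a few lines of wording, with no new data, visits or patients. The small downside is that more contrasts are always reported, and the correction over visits does not cover the separate overall group test. The supportive label is there for that reason.
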